### **5.2 Evaluating AEs and SAEs**

All AEs and SAEs will be evaluated in terms of the following items:

- Duration - start date and stop date
- Intensity - mild, moderate, or severe
- Causality - relationship between study medication and occurrence of each AE/SAE
- Outcome - resolved, resolved with sequelae, not resolved, unknown, death
- Action taken with study medication - none, discontinued, interrupted, unknown

### **5.3 Reporting of SAEs and Other Significant Events**

Investigators are obliged to notify, by fax (or telephone), to the sponsor all serious adverse events and unexpected suspected adverse drug reactions IMMEDIATELY (within 24 hours of the investigator becoming aware of the event). The investigator will be requested to supply as much detailed information regarding the event that is available at the time of the initial contact. The investigator is also required to submit follow-up reports to the monitor until the adverse event has resolved or in the case of permanent impairment, until the adverse event stabilizes.

ANY SERIOUS ADVERSE EVENT WHETHER OR NOT RELATED TO THE STUDY DRUG MUST BE REPORTED IMMEDIATELY TO THE FOLLOWING PERSON:

ProductLife

[contact]

E-mail: [[contact]](mailto:[contact])

For all SAEs a Serious Adverse Event Report Form that includes a detailed written description should be faxed to the above mentioned fax number, within 48 hours.

The responsible pharmacovigilance officer will immediately evaluate the SAEs for reporting to the appropriate regulatory agencies in consultation with the medical responsible person from the sponsor.

All serious, unexpected and related adverse events must also be reported to the reviewing IEC by the investigator. Confirmation that these reports have been submitted to the ethics committees must be forwarded to the monitor.

A Serious Adverse Event (SAE) is defined as any untoward medical occurrence that at any dose:

- results in death;
- is life-threatening (see Note);
- requires in-patient hospitalization or prolongation of existing hospitalization;
- results in persistent or significant disability/incapacity;
- is a congenital anomaly/birth defect.

Note: the term “life-threatening” refers to an event in which the patient was at risk of death at the time of the event; it does not refer to an event which hypothetically might have caused death if it were more severe.

Medical and scientific judgment should be exercised in deciding whether expedited reporting is appropriate in other situations, such as important medical events that may not be immediately life-threatening or result in death or hospitalization, but may jeopardize the patient or may require intervention to prevent one of the other outcomes listed in the definition above. These should also usually be considered serious. Also serious events which could be associated with the trial procedures (rather than with the IP) will be reported as SAEs, even if occurring outside the treatment procedure.

Under this protocol, the following event(s) will not be considered as (an) SAE(s) and should not be entered on the SAE form:

Pre-planned hospitalizations for diagnostic, therapeutic, or surgical procedures for a pre-existing condition that did not worsen during the course of a clinical trial. These pre-planned hospitalizations must be entered on the medical history form, including the condition requiring hospitalization. These events will, if applicable, still be reported as an AE.

Companion Diagnostic BV or its representatives will report all Suspected Unexpected Serious Adverse Reactions (SUSAR: SAEs that are unlisted and associated with the use of the drug) to the investigators, the Independent Ethics Committee (BEBO), the regulatory authorities (CCMO), and the CBG (College ter Beoordeling van Geneesmiddelen) within 24 hours.

The SUSAR report will contain the following information:

- the Eudract number of the study and the sponsors protocol study name and study number in which the SUSAR has taken place;
- the identification number which the investigator has given the SUSAR;
- the name and address of the person whom has reported the SUSAR;
- a description of why the SUSAR is suspect;
- a description of the study trial medication which suspectedly caused the SUSAR;
- the subjectcode, age and gender of the subject whom has had –or is having- the SUSAR;
- a description of the SUSAR, of it's course/the course of events, and a description of the treatment thereof/ the action taken;
- an assessment of the (consequences of) the SUSAR by the investigator for the (ongoing) clinical study;
- any other relevant information regarding the SUSAR.

## 6 STATISTICAL METHODS

The described analyses in this Chapter will be fully described in the Statistical Analysis Plan (SAP CD001).

### 6.1 Determination of Sample Size

MedCalc software (MedCalc Statistics for Biomedical Research 12.7, Ostend, Belgium) was used for the ROC curve power analysis. Assuming balanced design of 75 cases in the positive group and 75 in the negative group, giving a total of 150 cases, resulted in 90% statistical power to be able to detect a minimum AUC of .650 from the null hypothesis value 0.5 (meaning no discriminating power) with an  $\alpha$ -level of .05. The distribution of subjects among the groups was based on previous studies, in which the demarcation formula reliably allocated around 50% of all subjects (with complete screening data) to either group. In the Lybrido(s) Phase IIb studies (EB82 & EB90), 48% was marked as low sensitive and 52% as having high inhibition. This, combined with the theoretical background of the subdivision of these subjects (discussed earlier in the protocol), justifies these number in the power calculation.

The assumed AUC of .650 means that a randomly selected person from the positive group has a higher self-reported number of satisfying sexual events than that for a randomly selected person from the negative group 65% of the time. This assumption is considered realistic from an earlier study as stated above, where the correlation between the demarcation formula and another similar measurement of satisfaction was .83.

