## **2.2 Hypotheses**

### **2.2.1 Validation of existing demarcation formula**

In the present study, the existing demarcation formula will be validated. Its predictive power for Lybrido and Lybridos sensitivity will be measured using the subjects number of satisfying sexual events on Lybrido and Lybridos as compared to Placebo in the domestic setting in 150 healthy female subjects with FSIAD.

- Women with a low sensitivity (as compared to high sensitivity) for sexual cues as determined by the present demarcation formula will have a statistically significant higher number of satisfying sexual events in the Lybrido regime as compared to the placebo and Lybridos treatments;
- Women with a high sensitivity (as compared to low sensitivity) for sexual cues as determined by the present demarcation formula, will have a significantly higher number of satisfying sexual events in the Lybridos regime as compared to the placebo and Lybrido regimes.

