#### Primary Endpoint Analyses

- Differences in Lybrido-effect and Lybridos-effect between groups will be analyzed with two-way mixed design ANOVA- with 2 within subjects effect variables (Lybrido-effect *versus*

Lybridos-effect) x 2 between subjects group variables (Low Sexual Attention versus High Sexual Attention. The dependent variables are the effect variables Lybrido-effect and Lybridos-effect. ;

- To evaluate the quality of performance of the present demarcation formula for the identification of the Lybrido and Lybridos respondents, a receiver operating characteristic (ROC) curves analysis will be performed. For the true status of the women a classification of women into low sexual attention versus high sexual attention will be made based on the Lybrido- and Lybridos-effect variables: when the score on the Lybrido-effect variable is higher than the score on the Lybridos-effect variable, a women is classified as having low sensitivity for sexual cues and vice versa. For the predicted status of the women the present demarcation formula is used. By using different cut-off values of the present demarcation formula, a ROC curve is constructed and the AUC is derived.

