### **Exploratory analyses**

Summary statistics will be described for the FSDS-R, PGI-I and PBE data.

The level of statistical significance will be set at  $p < 0.05$ , one-sided. Data will be presented as mean  $\pm$  standard error of the mean. All statistical analyses will be conducted using IBM SPSS Statistics for Windows (Version 19.0. Armonk, NY: IBM Corp.).

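### The 90% power is right for the ROC AUC, but it is not power for the section 2.2.1 hypotheses, and the two primary analyses do not test whether the matched drug beats the other drug within each formula group

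*Protocol*

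**What the plan says.** Section 2.2.1 of the protocol, on validation of the existing formula, states two directional hypotheses. Low-sensitivity women are to have a "statistically significant higher number of satisfying sexual events in the Lybrido regime as compared to the placebo and Lybridos treatments". High-sensitivity women "will have a significantly higher number of satisfying sexual events in the Lybridos regime as compared to the placebo and Lybrido regimes". Each bullet also contains a parenthesis comparing the group with the other sensitivity group.

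Section 6.1 sizes the trial on one ROC curve. The layout is given as "Assuming balanced design of 75 cases in the positive group and 75 in the negative group, giving a total of 150 cases", and this "resulted in 90% statistical power to be able to detect a minimum AUC of .650 from the null hypothesis value 0.5". The section explains an AUC of .650 as a 65% chance that "a randomly selected person from the positive group has a higher self-reported number of satisfying sexual events" than a random woman from the negative group.

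Section 6.3 names two primary analyses:
- **Mixed ANOVA.** "Differences in Lybrido-effect and Lybridos-effect between groups will be analyzed with two-way mixed design ANOVA", with drug effect (Lybrido-effect, Lybridos-effect) within subjects and formula group between subjects.
- **ROC analysis.** A woman's true status is the sign of her own Lybrido-effect minus Lybridos-effect, and the formula is the predictor.

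Section 6.1 gives alpha as .05 without saying how many sides. The only statement on this is at the end of 6.3, under the exploratory analyses, where the significance level is one-sided 0.05.

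**The concern.** The hypotheses are claims about drug against drug inside each group. The powered quantity and both named analyses are claims about a difference between groups. The placebo term cancels in Lybrido-effect minus Lybridos-effect, so the ANOVA interaction compares the mean Lybrido-minus-Lybridos difference in one group with that in the other. The ROC asks whether the formula score ranks women on the sign of that difference. Neither asks which drug is better, on average, within a group.

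The formula is meant to allocate women between two drugs. Section 2.3 ties benefit to allocation to the right drug, and section 2.1.5.2 foresees phase 3 and clinical use. Allocating both drugs is justified only if the preferred drug reverses between the groups. A significant interaction without reversal does not show that. A reader who takes the 90% as the chance of confirming section 2.2.1 would also be misled about how likely that is.

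**Working it through.** **Inputs.** From 6.1: 75 + 75 women, AUC .650 against 0.5, alpha .05. From the end of 6.3: one-sided 0.05. Not in the protocol, so assumed: normal data, equal SD of the within-woman drug difference in both groups, no dropout, and how the between-group contrast divides between the groups (varied below).

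**1. Reproduce the printed figure.** With Hanley-McNeil standard errors at 75 + 75, SE is 0.0473 under the null and 0.0447 under AUC .65. Power = Φ((0.15 − z × 0.0473) / 0.0447).
- Two-sided, z = 1.960: 90.0%.
- One-sided, z = 1.645: 94.7%.

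The printed 90% is therefore the two-sided AUC test.

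**2. Convert to a standardised difference.** d = √2 × Φ⁻¹(.65) = 1.414 × 0.3853 = 0.545 SD in (Lybrido minus Lybridos) between the groups.

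**3. Power for the section 2.2.1 drug-against-drug claims.** With an even split the group means are +0.272 and −0.272 SD. Each is a paired t test with n = 75, 74 df and noncentrality 0.272 × √75 = 2.36. The groups contain different women, so joint power is the product.

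| Split of d | Both contrasts, one-sided 0.05 | Both contrasts, two-sided 0.05 |
|---|---|---|
| 50:50 | 0.756² = 57% | 0.644² = 41% |
| 60:40 | 52% | 37% |
| 70:30 | 38% | 26% |
| 75:25 | 31% | 20% |

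The even split gives the maximum. Simulation agrees (about 56–58% and 40–42%). Taking the AUC as 6.3 defines it, with a continuous score against the sign of the drug difference, gives about 58% and 43%.

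**4. Sensitivity to the AUC.** At an even split, joint power is 88% one-sided (79% two-sided) at AUC .70 and 94% (89%) at AUC .72.

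**5. Significance without reversal.** Simulated trials with 75 + 75 women, interaction at two-sided 0.05:

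| Mean difference, low / high sensitivity (SD, positive favours Lybrido) | Interaction significant | Both within-group contrasts met (two-sided) |
|---|---|---|
| +0.272 / −0.272 | about 91% | about 41% |
| +0.545 / 0 | about 91% | 2.5% |
| +0.795 / +0.25 | about 91% | 0% |

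The 6.3 ROC behaves alike. With a continuous score and group means of about +0.77 and +0.23 SD, both favouring Lybrido, it was significant in 84–89% across three simulation runs.

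**The case against.** Four points deserve weight.

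- **The 90% is correctly labelled.** Section 6.1 says it is ROC power, and ROC is one of the named primary analyses. This stands: the figure is not wrong, and the fault is only that it does not cover the hypotheses.
- **The hypotheses can be read as an interaction.** The parentheses comparing one sensitivity group with the other support that reading, and the 90% would then fit. But the same sentences still require superiority over the other drug and placebo within the group, so the parenthesis adds a comparison and removes none.
- **The SAP may hold contrasts and a success rule.** It may. The point does not rest on their absence: hypotheses, sizing and named primary analyses disagree within the protocol.
- **AUC .650 is a minimum.** Section 6.1 cites an earlier correlation of .83 with a similar satisfaction measure, and joint power rises quickly above .650. This stands as a limit on the 57%/41%. The formula was built by an iterative search that used 41 patients with response data (2.1.5.2), so the correlation may be optimistic.

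A reader might infer that the trial would declare the formula validated when one drug suits everyone. The protocol does not support that. It writes no validation rule, so all that can be said is that both listed analyses could be significant. A mean advantage is also not universal: at +0.25 SD, about 40% of high-sensitivity women (Φ(−0.25) = 0.40) still do better on Lybridos. If every woman did better on Lybrido, the ROC would have no second class. The pilot table in 2.1.5.2 does show reversal between its matched cells (Lybrido 35.6% against Lybridos −11.6%; 10.4% against 30.6%), so the no-reversal case is a possibility, not a forecast.

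**Conclusion.** The concern holds as a mismatch between section 2.2.1 on one side and sections 6.1 and 6.3 on the other. The named primary analyses can both be significant while the hypothesis for one group is false.

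At the AUC the trial is sized for, the chance of confirming the two drug-against-drug claims is at most about 57% at the protocol's one-sided 0.05, or 41% two-sided on the basis that reproduces the 90%. These are ceilings for AUC .650 under normality, equal SDs, an even split and no dropout. Two-week event counts may not be normal, and section 4.2 says treated women are not replaced. Section 2.2.1 also requires superiority over placebo, which is not in these figures and can only lower them. They are not the trial's overall chance of success if the true AUC is higher.

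**What to change.** **Section 6.3.** Keep the interaction and the ROC. Add planned within-group contrasts matching 2.2.1: Lybrido against Lybridos and against placebo in low-sensitivity women, and Lybridos against Lybrido and against placebo in high-sensitivity women. Claim validation for assigning both drugs only if the contrasts hold in both groups. Because all are required, that claim needs no alpha split. If they hold in one group only, limit the conclusion to that group. A one-group conclusion has two chances to arise, so say in advance whether it is supportive or confirmatory, and control the error rate if confirmatory.

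**Section 6.1.** State that the 90% applies to the ROC AUC only and is two-sided. Beside it, give the joint power of the drug-against-drug contrasts (57% one-sided, 41% two-sided at AUC .650) with its assumptions, and note that the placebo comparisons are excluded.

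**Cost.** Wording, and contrasts on data already collected, with no extra patients. The price is a less favourable stated power and a stricter validation claim.

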### 6.2 Analysis Populations

All analyses will be done using the intention-to-treat set and using a per-protocol set of subjects. The intention-to-treat set is comprised of all randomized subjects except those who have stopped or completed the study without taking any trial medication. The per-protocol set of subjects consists of all subjects for whom the minimum amount of data for valid analysis has been collected. Exact definitions for these 2 sets are given in the SAP CD001.

### 6.3 Study Endpoints Analyses

#### Study Endpoints Analyses

Firstly, we start to differentiate two subgroups on the basis of their scores on the demarcation formula into low and high sensitive to sexual cues, which could affect different responses on Lybrido and Lybridos. Secondly, we will calculate two variables on the basis of the difference between the number of satisfactory sexual events (SSE's) during both drug conditions and placebo: *Lybrido-effect* = number of SSEs during Lybrido minus number of SSEs during Placebo; *Lybridos-effect* = number of SSEs during Lybridos minus number of SSEs during Placebo.

#### Primary Endpoint Analyses

- Differences in Lybrido-effect and Lybridos-effect between groups will be analyzed with two-way mixed design ANOVA- with 2 within subjects effect variables (Lybrido-effect *versus*

Lybridos-effect) x 2 between subjects group variables (Low Sexual Attention versus High Sexual Attention. The dependent variables are the effect variables Lybrido-effect and Lybridos-effect. ;

- To evaluate the quality of performance of the present demarcation formula for the identification of the Lybrido and Lybridos respondents, a receiver operating characteristic (ROC) curves analysis will be performed. For the true status of the women a classification of women into low sexual attention versus high sexual attention will be made based on the Lybrido- and Lybridos-effect variables: when the score on the Lybrido-effect variable is higher than the score on the Lybridos-effect variable, a women is classified as having low sensitivity for sexual cues and vice versa. For the predicted status of the women the present demarcation formula is used. By using different cut-off values of the present demarcation formula, a ROC curve is constructed and the AUC is derived.

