### **Endpoints**

#### Primary Endpoint

Change from placebo in frequency of satisfactory sexual events, following study medication intake, measured by the Sexual Event Diary (SED), item 4. This endpoint will be used for validation of the existing demarcation formula.

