#### **3.3 Endpoints**

##### **3.3.1 Primary Endpoint**

- The primary endpoint is the change from placebo in frequency of satisfactory sexual events, following study medication intake, measured by the Sexual Event Diary (SED), item 4 (this endpoint is used for both the primary and secondary objective above)

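### Placebo cancels from the terms that can validate the formula, so the placebo half of both primary hypotheses has no primary test

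*Protocol*

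**What the plan says.** Section 2.2.1 states one hypothesis per formula group. Low-sensitivity women "will have a statistically significant higher number of satisfying sexual events in the Lybrido regime as compared to the placebo and Lybridos treatments". High-sensitivity women "will have a significantly higher number of satisfying sexual events in the Lybridos regime as compared to the placebo and Lybrido regimes". Each sentence makes two comparisons: matched drug against placebo, and matched drug against the other drug.

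The endpoint in section 3.3.1 agrees with this: "The primary endpoint is the change from placebo in frequency of satisfactory sexual events, following study medication intake". The synopsis says the same.

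Section 6.3 defines Lybrido-effect as "number of SSEs during Lybrido minus number of SSEs during Placebo" and Lybridos-effect as "number of SSEs during Lybridos minus number of SSEs during Placebo". Two primary analyses follow:

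- a 2 x 2 mixed ANOVA: "Differences in Lybrido-effect and Lybridos-effect between groups will be analyzed with two-way mixed design ANOVA- with 2 within subjects effect variables", crossed with the low and high formula groups;
- a ROC analysis whose true status is set by comparing the two effects: "when the score on the Lybrido-effect variable is higher than the score on the Lybridos-effect variable, a women is classified as having low sensitivity", and the reverse for high sensitivity.

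Placebo is a factor level only in the conditional analyses of the new formula. Both of those compare placebo with Lybrido, and neither compares placebo with Lybridos. Section 6.1 bases the sample size on the AUC alone.

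**The concern.** Writing both outcomes as differences from placebo makes the analysis look placebo-controlled. But a comparison of two differences that share a subtrahend no longer contains it. The results that would be read as validating the formula, namely the interaction and the AUC, show which drug did better for which woman. They do not show whether the better drug did anything. A woman with fewer events on both drugs than on placebo still gets a true status as a Lybrido or Lybridos respondent.

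Section 2.1.5.2 foresees the formula in phase 3 and, after approval, in clinical use, and section 2.3 ties correct allocation to a better outcome. A reader of a positive result would take it that both parts of the hypotheses were tested. As written, one part was not.

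**Working it through.** **Inputs.** L, Ls and P are a woman's event counts on Lybrido, Lybridos and placebo (section 6.3). N = 150, AUC 0.650 against 0.5, alpha 0.05, power 90% (section 6.1). Significance is one-sided at 0.05 (end of section 6.3). The protocol gives no mean or SD for event counts.

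**1. The plan's own figure.** Hanley-McNeil standard errors with 75 + 75 women are 0.0473 at AUC 0.5 and 0.0447 at AUC 0.65. Power = Phi((0.15 - 1.96 x 0.0473) / 0.0447) = Phi(1.28) = 90.0%. This reproduces with two-sided alpha; one-sided 0.05 would give 94.7%. The figure concerns the AUC and says nothing about a drug-placebo contrast.

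**2. Algebra.** (L - P) - (Ls - P) = L - Ls. So:

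- within-subject effect: the mean of L - Ls;
- interaction: L - Ls in the low group against L - Ls in the high group;
- ROC true status: the sign of L - Ls.

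What keeps placebo is the average (L + Ls)/2 - P, compared between groups (main effect) or taken overall (grand mean).

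**3. What the remaining terms can show.** Let a and b be the mean Lybrido- and Lybridos-effects in the low group, and c and d those in the high group. The matched effects are a and d.

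- Group main effect: (a + b)/2 - (c + d)/2. If a = d = 1 and b = c = 0, it is 0.5 - 0.5 = 0, so it misses a real benefit in both groups.
- Grand mean: (a + b + c + d)/4. It is 0.5 in that case, and also 0.5 if only the unmatched drugs work (a = d = 0, b = c = 1).
- Interaction and grand mean together: (a - b - c + d) + (a + b + c + d) = 2(a + d). Both being positive implies only that the sum of the matched effects is positive. With a = 1.5 and d = -0.5 the sum is 1.0, although Lybridos is below placebo in its own group.

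**4. Numerical check.** One simulated trial, with L and Ls fixed and only the placebo column replaced:

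| Placebo column | Interaction F | AUC | t, Lybrido vs placebo, low | t, Lybridos vs placebo, high |
|---|---|---|---|---|
| as generated | 11.7766 | 0.6158 | 0.65 | -0.24 |
| plus 3 | 11.7766 | 0.6158 | -8.36 | -9.35 |
| all zero | 11.7766 | 0.6158 | 11.37 | 11.31 |
| random | 11.7766 | 0.6158 | -3.73 | -4.74 |

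**5. How often it could mislead (illustration only).** Assumed: 150 women, placebo mean 4 events per two weeks, Poisson counts with between-woman CV 0.5, interaction two-sided 0.05, AUC one-sided 0.05, ties dropped, 3,000 runs. The matched drug equals placebo, and the unmatched drug is worse by the amount shown.

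| Loss on unmatched drug | Interaction and AUC both significant | Both matched drugs significantly above placebo |
|---|---|---|
| 0.75 | 79% | 0.2% |
| 1.0 | 96% | 0.3% |
| 1.5 | 100% | 0.2% |

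These losses are 19%, 25% and 38% of the assumed mean. The one negative cell in the development table of section 2.1.5.2 (sexual satisfaction, n = 41) is -11.6%, for Lybridos in low-sensitivity women with the CC genotype. With a loss of that size and a mean of 3 (0.116 x 3 = 0.35 events), the interaction alone is significant in about 43% of trials two-sided and 55% one-sided.

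In that same cell Lybrido was at +35.6%, so the drugs differ by 35.6 + 11.6 = 47.2 points. Of these, 11.6 (about a quarter) come from Lybridos falling below placebo.

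**The case against.** The primary objective is to validate a formula that predicts sensitivity to one drug or the other. Section 2.1.5.2 says the formula was built on the difference in effect between the two drugs, with the loss of information accepted. For that question L - Ls is the natural target, and the interaction and AUC are apt. This stands, and both should be kept.

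A reader might infer that placebo is absent from the primary analyses altogether. It is not. The between-group main effect and the grand mean contain it, and so would separate low-against-high comparisons of each effect, which the ANOVA wording allows. None of these tests a matched drug against placebo in its own group. For example, a low-against-high difference in Lybrido-effect can come entirely from the high group being below placebo.

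The hypotheses also carry a parenthesis comparing each group with the other, which permits a partly between-group reading. That makes the text less clear, but the comparison with placebo is still written into both sentences.

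Section 6 leaves full description to the SAP, which was not available for this review and may add simple-effect contrasts. It could do so, but the protocol itself names the primary analyses, and those do not match its hypotheses. This is a mismatch in the text, not a missing detail.

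Finally, the high rates in the simulation need a large loss on the unmatched drug and no effect of the matched one. The development cells with concordant markers show matched gains of 30.6% and 35.6%. The rates are therefore scenarios, not forecasts.

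**Conclusion.** The mismatch is real. Placebo has weight exactly zero in the interaction, the within-subject effect and the ROC true status, whatever the data. The terms that retain it do not answer the matched-group question. The placebo comparison in both hypotheses of section 2.2.1, and the change-from-placebo endpoint, therefore have no corresponding primary test.

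A positive interaction or AUC could arise solely from the unmatched drug doing worse than placebo. The frequency is unknown: under the assumptions above it runs from about 43% (interaction alone, loss of 11.6%) to nearly 100% (loss of 1.5 of 4 events).

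A reader might go further and infer that the trial would declare the formula validated with no benefit to anyone, or that the chosen analyses are wrong. The documents support neither. The protocol states no rule for declaring validation, and the analyses do serve the narrower question of which drug suits which woman.

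**What to change.** Keep the 2 x 2 interaction and the ROC analysis as the test of relative drug choice. Add an analysis of the event counts on all three regimens by formula group, with four named contrasts:

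- low group: Lybrido minus placebo, and Lybrido minus Lybridos;
- high group: Lybridos minus placebo, and Lybridos minus Lybrido.

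Treat a drug's hypothesis as supported only if the interaction and both of its matched-group contrasts are positive. If both drugs must succeed, no alpha adjustment is needed. If either may be claimed alone there are two chances of a false claim, up to 1 - 0.95^2 = 9.75% at one-sided 0.05 when the interaction is real but neither matched drug beats placebo. A rule such as Holm across the two drugs is then required.

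The alternative is to remove placebo from the hypotheses and limit the conclusion to relative drug choice.

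The cost is mainly wording, since the placebo data are collected anyway, but the claim becomes harder to win. In the same simulation model, with the matched drug adding 0.75, 1.0 or 1.5 events and the unmatched drug none, both matched-group placebo tests (one-sided 0.05) succeed in 48%, 77% and 98% of trials. The interaction and AUC together succeed in 70%, 89% and 99%. The full rule can do no better than the lower of the two. The protocol should state that its 90% power does not apply to the placebo contrasts.
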